## **7.2 Self-report questionnaires**

### **7.2.1 Self-report of symptoms and disorders**

- *Obsessive-Compulsive Inventory – Revised* (OCI-R) (91). The OCI-R is an 18 items self-rating scale, measuring six different symptom dimensions of OCD. The OCI-R total score has high test-retest reliability and high sensitivity to change, in relation to the Y-BOCS (92).
- *Dimensional Obsessive Compulsive Scale Short-Form (DOCS-SF)* is a self-report questionnaire adapted from DOCS (93). It consists of a symptom checklist covering obsessive and compulsive thoughts about “contamination”; “responsibility for harm, injury or bad luck”; “unacceptable obsessional thoughts”; “symmetry completeness and exactness”. For all dimensions five items on scale from 0 to 8 assesses severity: (a) time occupied by obsessions and compulsions, (b) avoidance behavior, (c) associated distress, (d) interference with daily functioning, and (e) difficulty disregarding obsessions and refraining from the compulsions. Item A and E is split into two questions. The total score ranges from 0 to 40.
- *Generalized Anxiety Disorder Assessment 7* (GAD-7) (94-96) is a brief 7-item self-report measure for generalized anxiety symptoms. Although developed for measuring severity of generalized anxiety disorder, the GAD-7 measures severity of general anxiety symptoms common to several anxiety disorders. The GAD-7 has been demonstrated to have good psychometric properties.
- *Patient Health Questionnaire*, (PHQ-9) (98-101) is a 9-item self-report questionnaire measuring level of depressive symptoms. Items are scored on a scale from 0 (not at all) to 3 (nearly every day). The PHQ-9 has been validated for clinical use and shows sound psychometric properties with high test-retest reliability.
- *The Bergen Insomnia Scale* (BIS) (77) will be used to screen for sleep disturbances. The scale has six items covering different aspects of sleep disturbances the past 4 weeks. The scale has acceptable psychometric properties (77)
- *Record of concomitant drug/medication* use during the period of the study will be recorded on a specially designed sheet.

- *Nijmegen Motivational List 2 (NML-2)* is a 25-item questionnaire assessing how the disorder impacts on the patients, motivation for treatment and beliefs about the present form of therapy. It has acceptable psychometric properties (105).

### 7.2.2 Treatment characteristics

- *The Treatment Credibility Scale (TC)* assesses how credible the participants perceive the treatment to be and how much they expect that they will improve from the treatment. The first four items are rated on a 0-10 point scale, and the last rated in percentage (0-100%), higher scores indicating higher credibility ratings.
- *Evaluation of treatment.* (See section 7.1; Assessor administrated measurements.)
- *The Working Alliance Inventory (WAI-P)* (97) is a 12-item questionnaire that assesses the therapeutic relationship. The WAI has good psychometric properties.
- *LET (Leaning in technique)* scoring sheet measures patient's cognitions and behavior during exposure, and whether they are actively trying to embrace the experienced anxiety or instead trying to hold back and down regulate it.
- *Client Satisfaction Questionnaire (CSQ-8)*(107) eight-item self-report form where patients report their level of satisfaction with the treatment they have undergone.
- *Patient Exposure and Response Prevention Adherence Scale (PEAS)* (108) is a three-item scale where patients and clinicians separately report the quantity and how exposure and response prevention was performed. It has good psychometric properties, and has been shown to predict the efficacy of ERP (109).
- *Prioritized exposure tasks* is a specially designed worksheet where the patient records what he or she finds the most anxiety provoking in order to individually tailor the treatment for each patient.
- *Daily recording of exposure tasks* is a specially designed worksheet which the patient fills out each day for three consecutive weeks, and the logs are to be returned on a weekly basis. Each day the patients reports on seven different questions about the obsessive-compulsive disorder, compliance to homework and self-guided treatment progress. (16).

### 7.2.3 Personal characteristics

- *The Client Socio-Demographic and Service Receipt Inventory (CSSRI)* (102) records socio-demographic data as well as previous treatment history. This is a comprehensive self-report measure which registers service utilization and cost of treatment for people with mental disorders.
- *Number of previous treatments* is a worksheet asking the patient to fill out information about any previous treatments for OCD, and the characteristics of the previously received treatments.
- *Onset and duration of disorder* is a specially designed worksheet where the patients record the onset and duration of his/her OCD.

- *Personality Inventory for DSM-5 Brief Form (PID-BF)* is a recently developed personality inventory, which is aimed at assessing dimensions in personality and personality disorders (110).
- *The Warwick-Edinburgh Mental Well-being Scale (WEMWBS)* (104) will be administered to assess mental well-being. This scale has 14 items covering different aspects of mental health related to mental well-being. The WEMWBS has shown good psychometric properties.
- *The Work and Social Adjustment Scale (W & SAS)* (103) is a short questionnaire measuring work status and social adjustment. The scale has good psychometric properties.
- *The Highly Sensitive Person Scale (HSPS)* (80) is a self-report questionnaire which measures aspects of sensitivity towards internal and external stimuli. The psychometric properties of the scale have been evaluated, demonstrating the scale's reliability and validity.
- *The Dispositional Resilience Scale – Revised (DRS-15-R)* (79) is a 15-item self-report instrument measuring resilience to challenges and life-stress. The Norwegian version of the instrument has good psychometric properties (111).
- *The Brief Illness Perception Questionnaire (BIPQ)* (78) will be administered to record illness perception. Although originally developed for measuring perception of somatic illness, the BIPQ has also been adapted to measure perceptions of mental health. The scale has sound psychometric properties.
- *Behavior Rating Inventory of Executive Function – Adult Version (BRIEF-A)* (82) consists of a self-report questionnaire filled out by the patient, and an informant questionnaire filled out by someone in the immediate family of the patient, each consisting of 75 items. It measures several executive functions: inhibition, ability to shift attention, emotional control, self-monitoring, ability to initiate, working memory capacity, ability to plan/organize, task monitoring and organization of materials.

### **7.3 Behavioral test**

During each exposure, the patient will be encouraged to approach the anxiety-triggers and taught how to do this without hesitation or “holding back”, and rather “lean into the anxiety” (LET-technique). A standardized procedure has been developed including self-report measures of “holding back”. The first exposure will be video-taped, as well as the final in which the patient will decide upon the most challenging trigger to be approached and scored by independent raters.

During the exposures the patients will rate how much they are “holding” back from the exposures, using a LET scale (0-100 where 0 indicate no “holding back”).

### **7.4 Neuroimaging**

Patients at the Bergen site of the study will be asked to undergo brain scanning using structural and functional magnetic resonance imaging at Haukeland University Hospital on the day before treatment, one week after the initial scan and at 3-month follow-up. The scanning procedures will be similar as those of an already approved protocol for non-relapsed OCD patients (REK reference 2015/936/REK Sør-Øst C).

## 8. Procedural consistency

The OCD-team leader at each site will serve as a contact person for the administrative leader of the project to ensure that all practical issues are taken care of.

### 8.1 Project organization

Project organization has been established.

### 8.2 Recruitment and attrition

Standardized study description forms and screening instruments will be used. Refusal rates, attrition rates and reasons will be monitored and compared quarterly.

Before the informed consent is signed, all eligible patients will be presented both with written information as well as watch a video introducing the study. They will be informed that final inclusion is decided upon by the national team of assessors (see below).

After informed consent has been provided and clinical information has been gathered and reported to the investigators using a standardized form, this information will be provided to a national team of assessors who meet weekly. They will assess if the person meets formal inclusion/exclusion criteria in terms of diagnostic criteria, prior Y-BOCS scores and the other inclusion/exclusion criteria listed. Questionable cases will be evaluated in greater detail by two senior investigators, who after reaching consensus will give the final decision of inclusion or exclusion, similar to what has been done in other large-scale studies (112, 113).

### 8.3 Self-report measures

The self-report measures will either be administered by paper and pencil or using online questionnaires in accordance with the official Norwegian regulations. All self-report measures will be administrated by a specially designated team who will monitor responses on a daily basis.

### 8.4 Therapist conducted screening and assessment

All Y-BOCS and SCID interviews for DSM-5 will be conducted by specially trained and independent assessors, blinded for the study-medication.

The following procedures for training of assessors will be employed:

1. The trainees receive theoretical lessons in how to use the scales.
2. The trainees receive practical instructions and video-demonstrations that illustrate different scores on the different items on the scales.
3. Each trainee receives three videotaped interviews which they rate. In order to proceed, the candidate has to demonstrate a minimum of 80 % "accuracy" (compared to an expert) on 2/3 of the interviews. On SCID it is suggested to employ a kappa-value of 0.80 and on YBOCS a maximum difference of  $\pm 2$  points.
4. When step #3 is completed, the trainee has to perform three live interviews with OCD-patients. These will be video-taped and rated by a blinded expert. The requirements are the same as on Step #3.
5. When Step #4 is completed, the assessor can start doing study-interviews.
6. All interviews are taped. Adherence checks will be performed on the 20 first interviews, and afterwards for 20% of the taped interviews. The checks will be conducted monthly and feedback will be given to the assessors. Significant disparities will be corrected through additional interviewer training and adherence monitoring.

Clinical interviews as well as CGI and GAF are administered by a specially trained psychiatrist or psychologist from the local OCD-teams.

### **8.5 Therapist competence and compliance**

All the 4-day treatment groups are led by two experts on the 4-day format together with OCD-therapists who must have participated in the extensive national training program (24) or document equivalent level of training.

In each treatment group the ratio between patients and OCD-therapists will be 1:1 and two experts on the 4-day concentrated format (cET) will participate in each group, which implies direct observation of the therapists.

In order to qualify as a cET-expert, therapists must in addition to being an OCD-therapist, have participated and received supervision in a minimum of two cET groups and demonstrate competency in the exposure procedure in accordance with the OCD CORE competencies (Steketee, Foa and Kozak, 2010) relevant for the 4-day format evaluated independently by two cET experts. Specific competencies required for the 4-day format will be recorded and evaluated separately. Evaluation of competency of the 4-days experts will be repeated every 6 months by the aims of video-taped role-played scenarios as well as multiple choice tests covering typical scenarios which will be rated independently by two cET-experts.

During the study, all therapists participating will be evaluated both for competency and adherence independently by the two cET experts who participate in the group each day. Relevant items in the OCD CORE competencies form will be employed, and the evaluation will be done at the end of each of the two days with exposure. Feedback to the therapists will be provided each day, and if the competence of a given therapist is not acceptable, the therapist will be required to act as an observer the remaining time of the group.

### **8.6 Intervention: The concentrated ERP-treatment combined with DCS-administration**

All included patients receive the same concentrated ERP (cET) treatment in combination with DCS or placebo. Therapists and participants are blinded to DCS or placebo randomization.

The patients will meet a GCP-trained assistant the second day of the intervention and receive 2 capsules of DCS or placebo. The first is to be taken after 3 hours of the cET. The participant also receives written information about capsule intake ordination and a telephone number if the participant has any questions or to report AE. The second capsule of DCS/ placebo is to be taken 1 h before cET Day 3.

For description of the cET see Havnen et al. (16, 59, 60). The cET format is based on standard ERP-treatment(114) employed in the national implementation project, but with a focus on actively “leaning into the anxiety” consistent with an inhibitory learning understanding of extinction.

The psychoeducation Day 1 will be delivered with the aid of a standardized PowerPoint presentation.

The psychoeducation for the families/ relatives (Day 3 of treatment) will be delivered with the aid of a standardized PowerPoint presentation.

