### **9.6 Treatment**

- **Day 1 Psycho-education and treatment preparation (3 h)**

Participants receive psychoeducation focused on the rationale behind the cET treatment which emphasizes the differences between this approach and the ERP they previously have received. Relevant exposure tasks will be decided upon. The patients are introduced to the micro-intervention “Leaning into the anxiety” (LET), which is to be practiced throughout the two days of exposure

- **Day 2 (8 hrs) and 3(8 h + 2 h psychoeducation for family): Therapist assisted Exposure and response prevention combined with DCS/ placebo**

Patients will engage in individually tailored and therapist assisted ERP, using the micro-intervention LET. Exposures will be conducted in a variety of settings with high ecological relevance, most of them out of the office. DCS on day 2 (first day of exposure) will be taken after 3 hours of the cET. DCS on day 3 will be given approximately 1 hour before the first exposure session of the day.

On day 3 the patient’s family/ significant others are invited to a 2 h psychoeducation.

- **Day 4: Summarizing and relapse prevention**

Summarizing (“lessons learnt”) and planning self-exposures for the next three weeks. Focus will be on teaching the patients how to be “their own therapists. The patients are provided with written information covering procedures and times for upcoming assessments. The patients will, in a group setting, give structured feedback/ evaluation of the treatment at the end, and will prepare exposure tasks to be performed the first three weeks after the treatment.

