## **10. DCS/ placebo side effects**

The DCS will be administrated in two single dosages, and the patients will be randomized to receive either 100 mg or 250 mg. Both dosages are smaller than standard dosage when the drug is administrated for its original purpose.

Previous trials with DCS with doses of 25-250 mg have reported little or no side-effects of DCS compared to placebo (11, 117-119). One potential danger could be that DCS would produce

reversed effects, i.e. DCS could enhance fear learning instead of fear extinction. One study reported facilitation of reconsolidation of fear if DCS was given prior to a single recall trial, but after using several recall trials, it facilitated extinction (120). No other published reports have reported any reversed effects of DCS.

In order to control for possible interactions with antidepressants (121) patients will be stratified in accordance to whether they receive antidepressants or not.

The DCS will be taken at the clinic, administered by a designated person, and the patients will be together with the therapist for at least five hours after intake. This ensures both compliance as well as the possibility to record side effects. Patients will be in contact with the clinic weekly for the first three weeks after the DCS/placebo intervention, which further ensures recording of side effects.

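### Section 8.6 hands out both capsules on Day 2, which conflicts with the rule in sections 10 and 11.5 that staff administer every dose under observation

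*Protocol*

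**What the plan says.** All references are to the protocol.

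- **Section 8.6 (intervention)** gives the dispensing step. "The patients will meet a GCP-trained assistant the second day of the intervention" and "receive 2 capsules of DCS or placebo". The Day 2 capsule is due after 3 hours of treatment. The other "is to be taken 1 h before cET Day 3". With the capsules goes a paper instruction: "The participant also receives written information about capsule intake ordination". A telephone number for questions or adverse events is also supplied.
- **Section 9.6 (treatment)** gives the Day 3 timing in slightly different terms: "DCS on day 3 will be given approximately 1 hour before the first exposure session of the day".
- **Section 10 (side effects)** sets the intake rule: "The DCS will be taken at the clinic, administered by a designated person". It adds that "the patients will be together with the therapist for at least five hours after intake" and draws the conclusion: "This ensures both compliance as well as the possibility to record side effects".
- **Section 11.5 (compliance)** repeats the rule. Designated personnel administer the drug to secure compliance, and the patient takes it with the therapist watching.
- **Section 11.6 (accountability)** says that investigators dispense by methods set out further on. No section from 11.7 to the appendix sets any out.
- **Section 11.10 (safety)** plans a face-to-face safety assessment on both drug days.

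**The concern.** Sections 10 and 11.5 make no exception for any day. If they are followed, staff control each capsule until the moment it is swallowed. Section 8.6 works differently for the second capsule: it passes to the patient the day before it is due, with written directions, and the only meeting with the assistant that 8.6 describes is on Day 2. Because the forward reference in 11.6 leads nowhere, 8.6 is the only hand-over procedure that a site can find in the protocol.

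What is at stake is whether the compliance and side-effect assurance is true for half of a two-dose regimen. The background section argues that DCS has no benefit of its own and works only in conjunction with extinction training, so whether and when the Day 3 capsule was taken is part of the intervention itself. The other safeguards do not fill the gap:

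- The rule in 11.7 on declining the drug names Day 2 only.
- Sections 5.3 and 5.4 cover discontinuation and its recording, but would not reveal a capsule that was silently skipped.
- Collecting leftover capsules under 11.6 can show that one was returned. It cannot show when, or before whom, another was taken.

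**Working it through.** The plan states no figure to reproduce. The check sets the sections side by side and compares the timings.

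**Step 1: who holds and who gives each capsule**

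| | Day 2 capsule | Day 3 capsule |
|---|---|---|
| Handed over (8.6) | Day 2 | Day 2 |
| Due (8.6) | 3 h into treatment | 1 h before cET |
| Due (9.6) | 3 h into treatment | about 1 h before the first exposure session |
| Place or observer in 8.6 | none named | none named |
| Place and observer in 10 and 11.5 | clinic, designated staff, therapist | clinic, designated staff, therapist |

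Section 8.6 is equally silent on the observer for both capsules, but the consequence differs. The Day 2 capsule falls inside a therapist-led session, so its timing alone puts the patient under observation. For the Day 3 capsule the timing may not do so, which is checked next.

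**Step 2: Day 2 timing**

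Section 9.6 gives 8 h of treatment and intake is after 3 h, so 8 − 3 = 5 h with the therapist remain. This is exactly the minimum in section 10. The Day 2 capsule fits the supervised model.

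**Step 3: Day 3 timing**

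Let the 8 h of Day 3 start at time 0, and let the first exposure session start x hours later. The protocol does not give x, so a range of 0 to 1 is shown as an assumption.

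- If cET in 8.6 means the start of the day, intake is at 0 − 1 = −1 h. It then falls 1 h before any scheduled therapist time.
- If it means the first exposure session, as 9.6 says, intake is at x − 1. The time between intake and the first scheduled contact is max(0, 1 − x):
  - x = 0 gives 1 h
  - x = 0.5 gives 0.5 h
  - x = 1 gives 0 h

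The interval before scheduled contact is therefore between 0 and 1 h, and the protocol does not settle which.

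**Step 4: therapist time after the Day 3 intake**

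Scheduled time after intake is 8 − max(0, x − 1). For x from 0 to 1 this is 8 h, above the five hours in section 10.

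**Step 5: share of the study drug**

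One of two capsules is concerned: 250 of 2 × 250 = 500 mg, 100 of 2 × 100 = 200 mg, or one of two placebo capsules.

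**Step 6: travel**

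Section 5.2 excludes patients who live more than an hour away, so eligible outpatients may travel for up to an hour. If intake is due an hour before the day starts, a patient who arrives for the start could still be on the way. This is an inference, since no arrival time is given.

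**The case against.** The strongest reply is that 8.6 is merely silent. It fixes when capsules are handed over and when they are due, and sections 10 and 11.5 supply the place and the observer for all doses. Receiving a capsule on Day 2 and swallowing it before staff on Day 3 are compatible, and a site that obeys every section must observe the second intake. The passive wording of 9.6 suggests that staff give the dose, and 11.10 plans staff contact on Day 3. The written information is weak evidence of self-dosing, because it also accompanies the supervised Day 2 capsule.

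Much of this stands, and it limits what can be said. A reader might infer any of the following, and the documents do not support them:

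- **That the protocol permits unobserved dosing at home.** Nowhere does it say so, and 9.6 and 11.10 point the other way.
- **That no therapist is available at the Day 3 intake.** This holds only if cET in 8.6 means the start of the day, or if exposure begins less than an hour into it.
- **That the five hours in section 10 are breached.** Section 10 asks for at least five hours with the therapist after intake, and step 4 gives 8 h. Requiring the first five hours to be covered without a gap would be stricter than that text.
- **That intake times go unrecorded.** The CRF is not shown, so this cannot be known.

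What does not stand is that nothing needs correcting. Section 8.6 takes a positive step, giving the patient the next day's dose, and that step does not fit a rule under which staff administer each dose. Section 9.6 names neither place nor observer, and 11.10 does not tie its safety assessment to the moment of intake. One site could follow 8.6 and another 11.5, and both could believe that they complied.

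**Conclusion.** The point holds as a conflict between the dispensing step in 8.6 and the intake rule in 10 and 11.5, for one of two capsules per patient. The Day 2 capsule is not affected. The textual conflict needs no assumption beyond reading 10 and 11.5 as covering every dose, which is how they are written. Whether supervision would actually be missing on Day 3 is open: it depends on the meaning of the start of cET, on x, and on site practice that the protocol does not show.

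The protocol gives no rate of missed or mistimed doses, so no effect on power or bias is computed or claimed. The correction is still worth making, because supervised intake is the protocol's stated ground for compliance and for the recording of side effects, and 8.6 followed literally would make that statement untrue for the second dose.

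**What to change.** Amend 8.6 so that the patient receives only the Day 2 capsule on Day 2. Staff keep the second capsule and give it under observation at the clinic, about 1 h before the first Day 3 exposure session. This brings 8.6 into line with 9.6, 10 and 11.5 and removes the ambiguity about the start of cET. Replace the forward reference in 11.6 with a pointer to 8.6.

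If take-home dosing is what the sponsor intends, say so in 8.6 and limit the compliance statements in 10 and 11.5 to Day 2.

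The cost is one or two sentences and a cross-reference. In practice, some patients and one staff member may have to arrive up to an hour earlier on Day 3.
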